## Abstract

**Background:** The Republic of the Marshall Islands has the highest prevalence of type 2 diabetes (T2D) in the world, with the country's rapid rise of T2D attributed to its reliance on imported and refined foods laden with salt, sugar, and fat. As much as lifestyle factors can increase the risk of T2D, they can also reverse or treat the disease, with multiple studies demonstrating that plant-based diets and/or moderate exercise improve glycemic control and cardiovascular risk factors in T2D patients.

**Objective:** We therefore tested the hypothesis that a community-based, intensive, plant-rich lifestyle intervention with exercise is more effective for treating and managing T2D in the Republic of the Marshall Islands than the standard of diabetes care.

**Methods:** Building on a successful lifestyle program used at the Guam Seventh-day Adventist Clinic, we conducted a randomized controlled trial to test the effectiveness of an intensive lifestyle intervention involving a plant-rich diet and moderate exercise or the standard of care in T2D patients for 24 weeks. In this manuscript, we describe the clinical trial protocol, including the rationale, design, and methods of the clinical trial and the lifestyle program. The lifestyle intervention included a step-wise, intensive 12-week program of counseling and instruction on healthy eating, exercise, and stress management. The prescribed diet focused on high-fiber, whole plant foods, with foods grouped into a four-tiered system. The lifestyle intervention also involved hands-on cooking classes, meals prepared for participants, and group exercise classes—all tailored to be culturally appropriate. The study's main endpoints were glycemic control and cardiovascular disease risk factors.

**Discussion:** The present study is the first randomized clinical trial conducted in the Republic of the Marshall Islands and the first lifestyle intervention trial conducted in Micronesia. The results of this study will help guide future medical care for indigenous populations in the Pacific Islands and will also shed light on how to effectively design and deliver intensive lifestyle interventions to treat and manage diabetes.

**Clinical Trials Registration:**
www.ClinicalTrials.gov; identifier NCT03862963

## Introduction

Diabetes is a rising epidemic. More than 420 million people worldwide have the disease (1), and new estimates suggest that diabetes now afflicts about 9.4% of Americans (2). Yet, in some countries, such as within the Pacific Islands and Micronesia, the prevalence of diabetes among adults is as high as 25–31% (3).

The Republic of the Marshall Islands (RMI) has the highest prevalence of diabetes in the world, where the disease afflicts almost one-third (31.4%) of all adults aged 18–99 years (3). The explosion in diabetes rates in the RMI is a relatively recent phenomenon. In the 1950's, only three people in the RMI were known to have the disease, according to an oral report by an RMI health official in 2005. By the 1990's, the prevalence had reached 30% (4). Now, more than half of all hospital admissions in the capital city of Majuro are due to diabetes (5), and 60% of deaths in adults under the age of 60 years are attributed to the disease and its related comorbidities (5). The epidemic has been attributed to the growing population, which has strained supplies of healthier indigenous foods and increased the reliance on imported goods such as flour, rice, and foods high in salt, sugar, and fats (6).

To combat the growing global diabetes epidemic, the American Diabetes Association has called for increased use of lifestyle interventions as part of primary care (7). Indeed, dietary interventions can lower hemoglobin A1c (HbA1c) by 0.5–2.0% (7), with several trials reporting values between 1.0 and 3.4% (8–20) as well as reductions in hyperglycemic medications and/or even T2D remission (8, 10–12, 15, 17, 19, 21–27). In particular, several trials suggest that vegetarian and vegan low-fat diets are superior to conventional diets for lowering glucose, HbA1c, and insulin levels; decreasing diabetes medication dosages; and reducing diabetes complications, such as neuropathy, in T2D patients (12, 19, 20, 22, 26–40). This is corroborated by prospective cohort studies, such as the Nurses' Health Study and Adventist Health Study-2, which report that plant-based diets reduce the risk of developing type 2 diabetes by about half (41–45). Moreover, among populations such as the Seventh-day Adventists, the prevalence of diabetes among vegans is as low as 0.22 times that among non-vegetarians (45, 46). Plant-based diets have also been found to improve lipids, renovascular health, and oxidative stress levels in adults with T2D more effectively than conventional diets (12, 19, 22, 26, 28, 31–35, 38, 47). Plant-based diets likely mediate these effects through multiple mechanisms (47–49), including through improvements in body weight and visceral fat [e.g., (32, 36, 50, 51)]; insulin sensitivity and beta-cell function (32, 39, 52, 53); incretins and gastrointestinal hormones (39, 52); oxidative stress (32); phytochemical intake [including polyphenols and plant sterols (49, 54)]; fiber and prebiotic intake, which positively modulate gut microbiota (55); lower oxidant intake (such as heme iron) (49); and increased well-being (37). Lifestyle interventions that combine plant-diets with regular exercise may be even more effective. Coupling a plant-based diet with exercise significantly reduces the incidence of diabetes in glucose-impaired individuals (56, 57), and clinical trials show that the combination is effective for treating diabetes, cardiovascular disease, obesity, and other chronic conditions (32, 58–64). To date, however, only one previous clinical trial has combined a plant-rich diet with exercise for treating T2D (65).

Despite the promise of such lifestyle interventions, implementing them in indigenous populations such as the RMI presents unique challenges. Research has shown that such interventions are more effective when they are culturally-sensitive and delivered to communities, rather than to individuals or families (66). In the late 1990's, Canvasback Missions, Inc., recognized the need for such interventions in the RMI and conducted two lifestyle intervention programs with excellent results, using a modified version of the NEWSTART® wellness program operated by the Guam Seventh-day Adventist Clinic (67). The program emphasizes a whole-food, plant-rich diet with moderate exercise and is used to treat T2D, obesity, and other chronic diseases. Although no studies have been published on the intervention, Guam physicians have found it effective and continue to refer their patients to wellness centers (68).

Building on the success of these lifestyle intervention programs in Guam and the RMI, we designed and conducted the first randomized controlled trial to rigorously evaluate whether a comprehensive, culturally-sensitive, lifestyle intervention program can treat T2D in the RMI. The goal of the study was to determine the effectiveness of an intensive lifestyle intervention consisting of a mostly plant-based diet and regular moderate exercise in Marshall Islanders with T2D. The present study was also the first randomized clinical trial ever conducted in the RMI and the first lifestyle intervention trial ever conducted in Micronesia. The primary aim was to determine whether the lifestyle intervention can improve glycemic control. The primary endpoints included fasting glucose, fasting insulin, HbA1c, insulin resistance as measured by the Homeostatic Model Assessment of Insulin Resistance (HOMA-IR), and usage of diabetes medications. The secondary aim was to determine whether the lifestyle intervention could improve cardiovascular risk factors, including lipids, blood pressure, heart rate, high-sensitivity C-reactive protein (hs-CRP), body weight, body mass index (BMI), and waist circumference. We hypothesized that study participants would be able to make sufficient lifestyle changes—including by modifying their diet and increasing their physical activity—to achieve clinically meaningful improvements in glycemic control and cardiovascular risk factors, relative to the control group.

## Materials and Methods

### Study Design

#### Study Overview

This trial was conducted in partnership with the RMI's Ministry of Health (MOH). The study was designed as an open-label, parallel-arm, randomized controlled trial and was conducted at the MOH's Diabetes Wellness Center (DWC) in the city of Majuro in the RMI. Adults with T2D were randomized to receive either the standard of diabetes care (control group) or a lifestyle intervention comprising a whole-foods, largely plant-based diet combined with increased physical activity (intervention group). The intervention group received intensive counseling, support, and group sessions over a 12-week period and then continued the lifestyle intervention on their own for the remainder of the 24-week intervention. Health outcomes were assessed at weeks 0 (baseline), 2, 6, 12, and 24. At the end of the study intervention, those who were randomized to the control group were offered the option to crossover to the experimental arm and complete the lifestyle program. The study was approved by the Loma Linda University Institutional Review Board (IRB #: 59105) and an *ad-hoc* Institutional Review Board in the RMI that was set-up specifically for the trial. The study was conducted in accordance with the Declaration of Helsinki. All participants provided written informed consent prior to enrolling in the study and were given a stipend for their participation. Due to the nature of the intervention, the study was not blinded.

#### Recruitment

During year 1 of the study, participants were initially recruited from the general public. Two local leaders assisted in building interest among and recruiting Majuro residents. During year 2, participants were recruited both from the general public and from the MOH Diabetes Clinic through its diabetes registry. Of those screened, 18% or 31 out of 169 eligible participants dropped from the trial before beginning the intervention. The first cohort began the study intervention in June 2006 and the last cohort began in July 2008. Due to a lack of funding after the clinical trial ended, the study data was not analyzed and published until the present.

#### Eligibility Criteria

Recruited individuals were screened against a series of inclusion and exclusion criteria. The inclusion criteria were: (1) resident of RMI, (2) aged 18–75 years, (3) HbA1c ≥ 8.0% or diagnosed with T2D and taking diabetes medication, and (4) medical clearance to participate from DWC physicians. The exclusion criteria included (1) recent ( ≤ 3 months) change in a diabetes-related medication dosage, (2) a physical or medical condition that would impede participation in the lifestyle intervention (e.g., wheel-chair bound, unstable angina), (3) evidence of significant coronary heart disease, and (4) previous participation in an intensive lifestyle intervention. There were no eligibility criteria related to BMI.

#### Screening

Prospective participants were screened during a single in-person visit, which included a review of their medical history, physical fitness testing, a dietary assessment based primarily on a food frequency questionnaire, and fasting blood draws to measure glucose and HbA1c. Screening was performed at the DWC. To ensure suitability for the exercise portion of the intervention, participants were queried about their cardiovascular fitness and history. Those with ischemic heart disease were required to have special clearance from their physician. A physician reviewed all dietary, medication, and medical history data for medical clearance. Individuals who passed the screening process later attended an oral presentation explaining the study. During these group sessions, the study was explained to the participants in detail. Translators were assigned by the MOH to explain the study to participants who did not understand English. Interested participants then read and signed the informed consent in English or their native language.

#### Randomization

Following enrollment, participants were randomized to the two groups. Spouses who enrolled in the trial were randomized in pairs to keep them together. Non-eligible spouses were encouraged to attend counseling sessions but were not enrolled in the study.

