#### Cohorts

Participants were enrolled in five overlapping cohorts, with each cohort including both a control and intervention group (described below). Within each cohort, participants were randomized to one of the two groups in approximately equal numbers. The cohorts were spread over a two-year period, with Cohorts 1 and 2 finishing in year 1 and Cohorts 3–5 finishing in year 2. The cohorts 1–5 consisted of 27 (13 in the intervention group vs. 14 controls), 41 (21 vs. 20), 31 (9 vs. 22), 27 (14 vs. 13), and 43 (22 vs. 21) participants, respectively. The control arm received the usual standard of diabetes care, while the intervention arm received a lifestyle intervention. Unfortunately, not all participants in the control group in year 1 sought and received the usual standard of care for diabetes treatment as instructed, so starting in year 2, participants were primarily recruited from the MOH Diabetes Clinic, in order to ensure that the control group was compliant with the standard of care. Furthermore, to improve the delivery of the intervention, Cohorts 3–5 received an enhanced version of the lifestyle intervention. The enhanced version was identical to the standard version of the intervention, with the exception of more patient education and contact during weeks 4 and 6 of the study. The nature of the dietary and exercise intervention itself was not changed and did not vary across cohorts.

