## Data analyses

### Statistical Power Calculation

Since the trial proceeded in phases, the initial data collected in year 1 was used to determine the overall sample size needed for the trial. Based on the variances observed in the primary endpoints in the year 1 cohorts, a sample size of *N* = 120 in total was needed to provide at least 80% power (two-sided, α = 0.05) to detect between-group differences of 20 mg/dl in fasting glucose and 1.0% in HbA1c.

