### Statistical Analyses

All data will be analyzed using two-sided statistical tests and a Type I error rate of α = 0.05. The intention-to-treat method will be used for the primary analyses but will be compared to outcomes from actual-treatment-received analyses (i.e., per protocol analyses). Categorical data will be compared between the two groups using chi-square or Fisher's exact tests. Continuous data will be compared using linear mixed models or non-parametric tests (as appropriate), with potential adjustments for changes in medication dosages and potential covariates such as baseline values, age, biological sex, and cohort number. Likelihood functions will be examined to determine the appropriateness of covariates and to avoid overfitting the data. Multivariable linear and logistic regression will be used to identify predictors for improved health outcomes. Lastly, subgroup analyses may be performed by sex, age, co-morbidity, length of diagnosis, and severity to evaluate heterogeneity in treatment responses.

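### Enrolled spouses were randomised as pairs, but the categorical and rank tests named in the plan assume independent participants, and no couple term is named for the mixed models

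*Protocol article*

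**What the plan says.** On allocation, the Randomization section states: "Spouses who enrolled in the trial were randomized in pairs to keep them together". It adds that spouses who were not eligible could attend counselling but were not enrolled. The Cohorts section says that within each cohort "participants were randomized to one of the two groups in approximately equal numbers", and gives counts by cohort and arm. It does not say how many couples there were.

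On analysis, the Statistical Analyses section states: "Categorical data will be compared between the two groups using chi-square", with Fisher's exact test as the alternative. Continuous data go to linear mixed models or non-parametric tests. The potential covariates given as examples are baseline value, age, sex and cohort number. Neither couple nor household appears, and no random effect of any kind is specified.

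On endpoints, the Introduction lists use of diabetes medication among the primary endpoints. The Medications section plans a between-group comparison of the percentage of participants on at least one medication, for all medications and for diabetes medications separately.

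On sample size, the Statistical Power Calculation section says that 120 participants "in total was needed to provide at least 80% power", to "detect between-group differences of 20 mg/dl in fasting glucose and 1.0% in HbA1c". No allowance for pairing is mentioned.

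**The concern.** Two spouses who always go to the same arm do not provide two independent allocations. A test that counts them as two independent observations takes the variance of the arm difference to be smaller than it is whenever their outcomes are positively correlated.

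The article makes a positive correlation plausible. Spouses took part in cooking classes together, participants chose their own food when not eating centre meals, adherence waned later in the trial, and about a quarter of controls are thought to have changed their lifestyle. Two people sharing a kitchen would tend to adhere, lapse or take up the programme together. That would correlate their changes as well as their starting values, so baseline adjustment would not necessarily remove it.

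The plan sets a two-sided 5% error rate for all analyses. For the medication-use comparison it names tests that do not match the allocation. What is at stake is intervals that are somewhat too narrow and p-values that are somewhat too small, which matters mainly for borderline results.

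**Working it through.** **The plan's own figure.** N = 120 cannot be reproduced, because the section says only "Based on the variances observed in the primary endpoints in the year 1 cohorts" and gives no standard deviation. With 60 per arm, 80% power and two-sided 5%, the implied SD is difference / [(1.960 + 0.842) × √(2/60)] = difference / 0.5115. That gives 20 / 0.5115 = 39.1 mg/dl for glucose and 1.0 / 0.5115 = 1.955 percentage points for HbA1c, assuming independent participants and no allowance for loss.

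**Design effect.** Let f be the share of participants enrolled as one of a couple (taken as equal in both arms) and ρ the within-couple correlation. An arm of n participants contains fn/2 couples. The variance of the arm total is nσ² + (fn/2) × 2ρσ² = nσ²(1 + fρ). Hence:

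- Design effect: DE = 1 + fρ
- Shortfall in the unadjusted standard error: 1 − 1/√DE
- Actual Type I error of a nominal 5% test: 2 × [1 − Φ(1.96/√DE)]

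**Inputs.** Neither f nor ρ is in the article. Assumed ranges are f = 0.10 to 0.40 and ρ = 0.2 to 0.5. Of the 169 participants in the cohort counts, f = 0.10 means about 8 couples (169 × 0.10 / 2) and f = 0.40 about 34.

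| f | ρ | DE | SE too small by | Type I error |
|---|---|---|---|---|
| 0.10 | 0.2 | 1.02 | 1.0% | 5.2% |
| 0.10 | 0.5 | 1.05 | 2.4% | 5.6% |
| 0.20 | 0.2 | 1.04 | 1.9% | 5.5% |
| 0.20 | 0.5 | 1.10 | 4.7% | 6.2% |
| 0.40 | 0.2 | 1.08 | 3.8% | 5.9% |
| 0.40 | 0.5 | 1.20 | 8.7% | 7.4% |

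For example, f = 0.40 and ρ = 0.5 give √1.20 = 1.095, 1.96/1.095 = 1.789, and a two-sided tail of 0.0736.

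**Simulation check.** Ordinary two-sample t-tests with 60 per arm (40,000 replicates) gave 5.4% at f = 0.10, ρ = 0.2; 5.4% at 0.20, 0.2; and 5.7% at 0.20, 0.3. The formula gives 5.2%, 5.5% and 5.7%. With 169 participants (20,000 replicates), simulation gave 5.9% at 0.20, 0.5 and 7.6% at 0.40, 0.5, against 6.2% and 7.4%. The agreement is adequate.

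**Sample size.** The cohort counts sum to 79 intervention and 90 control, 169 in all. At the worst assumed DE of 1.20, 169 / 1.20 = 141 effective participants, with power of about 86% at the back-solved SD. If only the 169 − 31 = 138 who began the intervention contribute, 138 / 1.20 = 115 and power is about 78%; at DE = 1.10 it is about 82%.

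**The case against.** The strongest objection concerns scope. Glucose, insulin, HbA1c and HOMA-IR may all be analysed with linear mixed models, the usual vehicle for a couple effect. The article names no random effects at all, not even one for participant despite five visits, and its covariates are given as examples. Random-effects structure is commonly left to the full protocol or analysis plan. This stands: a reader might infer that the whole analysis treats participants as independent, but the article supports that only for the chi-square, Fisher's exact and standard rank tests. For the mixed models it neither includes nor excludes a couple term.

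Second, the number of couples may be small. Both spouses had to meet the diabetes, medication-stability and clearance criteria, and the article expects some spouses to be ineligible. Cooking classes with spouses may have involved people who were not enrolled. This also stands. It is why the range starts at 10%, where the inflation is close to negligible, and why the conclusion is conditional.

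Third, a reader might infer that the trial is underpowered or that the stated 80% is wrong. The documents do not support this: no SD is given, and 169 were allocated against 120 required. Power slips just below 80% only in the worst assumed case with 138 contributing.

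The objection does not remove the mismatch for categorical data. There the article does name the test, and that test ignores the pairing stated in its own Randomization section.

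**Conclusion.** The point holds in conditional form. Spouses were allocated as pairs. The chi-square, Fisher's exact and standard non-parametric tests do not allow for this, and the mismatch reaches the medication-use part of the primary endpoints. For the mixed models the gap is that a couple term is not named, not that one has been ruled out.

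The size depends on two quantities the article does not give. With 10–40% of participants in couples and a correlation of 0.2–0.5, unadjusted standard errors are about 1–9% too small and the Type I error is 5.2–7.4% instead of 5%. If few couples enrolled, or their outcomes are barely correlated, the effect is negligible. The couple count is needed to tell which case applies. The correction should be made because it is cheap and the analysis is still described in the future tense.

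**What to change.** - **Continuous outcomes in models:** include a couple-level random intercept, with single participants as clusters of one, or use couple-clustered robust standard errors. A participant-level effect for repeated visits does not replace it. With few couples the variance component may be estimated at or near zero, and the robust-error form is then the simpler choice.
- **Binary and rank comparisons:** use couple-clustered logistic or GEE models. Where cells are sparse, which is where Fisher's test would have been used, use a permutation test that permutes by randomisation unit (couple or single) within cohort.
- **Reporting:** give the number of enrolled couples per arm.

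The cost is slightly wider intervals and the work of identifying couples in the records, which may take effort given the record-keeping difficulties described in the Discussion. The Statistical Power Calculation section needs no change.

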#### Cohorts

Participants were enrolled in five overlapping cohorts, with each cohort including both a control and intervention group (described below). Within each cohort, participants were randomized to one of the two groups in approximately equal numbers. The cohorts were spread over a two-year period, with Cohorts 1 and 2 finishing in year 1 and Cohorts 3–5 finishing in year 2. The cohorts 1–5 consisted of 27 (13 in the intervention group vs. 14 controls), 41 (21 vs. 20), 31 (9 vs. 22), 27 (14 vs. 13), and 43 (22 vs. 21) participants, respectively. The control arm received the usual standard of diabetes care, while the intervention arm received a lifestyle intervention. Unfortunately, not all participants in the control group in year 1 sought and received the usual standard of care for diabetes treatment as instructed, so starting in year 2, participants were primarily recruited from the MOH Diabetes Clinic, in order to ensure that the control group was compliant with the standard of care. Furthermore, to improve the delivery of the intervention, Cohorts 3–5 received an enhanced version of the lifestyle intervention. The enhanced version was identical to the standard version of the intervention, with the exception of more patient education and contact during weeks 4 and 6 of the study. The nature of the dietary and exercise intervention itself was not changed and did not vary across cohorts.

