
In achieving these successes, we overcame several challenges. First, recruitment was slower than expected in year 1, so in year 2, we increased enrollment rates by recruiting subjects from the MOH Diabetes Clinic. Another benefit of this change in our recruitment strategy is that it improved compliance to the standard of care in the control group. During year 1, when participants were screened from the general public, they did not always adhere to the standard of care. Recruiting subjects who were already receiving the usual care and regularly met with their physicians resolved this problem. In year 2, as the word spread throughout the country that the DWC program was controlling and reversing T2D naturally, more and more people came forward and wanted to participate, and recruitment was no longer a challenge. In fact, by the end of the trial, more than 100 people were on the waiting list for the DWC program. Another challenge faced in year 1 is that about 25% of the adults screened did not comprehend English well enough to understand materials presented in English. This may have introduced selection bias by enrolling better-educated participants in year 1. Therefore, in year 2, all program materials were translated into Marshallese and presented in Marshallese, initially by translating English presentations, and then later by replacing English presentations with Marshallese presentations. Cohort 5 was the first all Marshallese-run program. After an initial hurdle of training local staff, who had little previous experience and limited education, to become precise and accurate recordkeepers and accurate presenters, we were able to deliver an all Marshallese-version of the intervention.

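### Cohort 3 is reported as 9 vs 22 although every cohort is said to have been randomised in roughly equal numbers; its allocation should be verified before analysis

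*Protocol article*

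**What the plan says.** The Cohorts section of the protocol article gives one allocation rule for all five cohorts: "Within each cohort, participants were randomized to one of the two groups in approximately equal numbers". It then lists the counts. Cohort 1 had 27 people, 13 of them allocated to the lifestyle programme and 14 to usual care. For cohorts 2 to 5 the article reports "41 (21 vs. 20), 31 (9 vs. 22), 27 (14 vs. 13), and 43 (22 vs. 21) participants, respectively". The first number in each pair is the intervention arm, so cohort 3 is 9 intervention vs 22 control.

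The Randomization section adds only that "Spouses who enrolled in the trial were randomized in pairs to keep them together"; the number of couples is not given. The Study Overview says: "Due to the nature of the intervention, the study was not blinded". Nothing in the article comments on the cohort 3 split.

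The Statistical Analyses section makes intention to treat primary, adds a per-protocol comparison, and names cohort number among covariates that may be used. It says nothing specific about cohort 3.

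**The concern.** A stated property of the design is contradicted by the counts that follow it in the same paragraph. The other four cohorts are balanced as tightly as an odd total permits, while cohort 3 has 29% of its members in the intervention arm.

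Several explanations are possible: a different but still random ratio in that cohort, an unlucky simple randomisation, wrong counts, or people moved or recorded in an arm other than the one first assigned. Only the last would damage the comparison. In an open-label trial it cannot be dismissed without looking, because staff and participants knew what each arm involved. If it happened, the cohort 3 contrast would be partly observational. Any selection would then enter the pooled treatment effect, and adjusting for cohort would not remove it.

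**Working it through.** **Inputs** (Cohorts section), intervention vs control: 13/14, 21/20, 9/22, 14/13, 22/21.

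**1. Do the counts add up?** Cohort totals are 27, 41, 31, 27 and 43, which sum to 169. The arms sum to 79 and 90, and 79 + 90 = 169. The Recruitment section uses the same 169 when it reports that "18% or 31 out of 169 eligible participants dropped from the trial before beginning the intervention". Two things follow:
- An isolated misprint in cohort 3 is unlikely, since a change to one figure would break the totals.
- The counts appear to include those lost before the intervention, so that loss does not seem to explain the split. This is inferred from the matching total; the article does not state it.

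**2. Cohort 3 alone, simple 1:1 randomisation.** The difference is 22 − 9 = 13, and 9/31 = 29%.
P(9 or fewer in either arm | n = 31) = 2 × Σ C(31,k)/2³¹ for k = 0 to 9 = 0.029.

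**3. Allowing for five cohorts.** In each cohort, take the least extreme split whose two-sided probability is at most 0.029: 0.019 (n = 27), 0.028 (41), 0.029 (31), 0.019 (27), 0.014 (43).
P(at least one) = 1 − (0.981 × 0.972 × 0.971 × 0.981 × 0.986) = 0.10.

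**4. Couples allocated as units.** The number of couples among the 31 is an assumption. The cohort 3 probability becomes:

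| Couples | 0 | 2 | 3 | 5 | 8 | 10 | 14–15 |
|---|---|---|---|---|---|---|---|
| P | 0.029 | 0.041 | 0.047 | 0.059 | 0.079 | 0.092 | 0.12 |

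**5. The tight balance elsewhere.** For odd n the smallest possible difference is 1, with P = 2 × C(n,(n−1)/2)/2ⁿ: 0.299 (27), 0.245 (41), 0.280 (31), 0.299 (27), 0.239 (43).
- Cohorts 1, 2, 4 and 5 all at the minimum: 0.299 × 0.245 × 0.299 × 0.239 = 0.005. These four are picked after seeing the data.
- At least four of any five at the minimum, which does not choose the odd one out afterwards: 0.021.

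Simple randomisation throughout is therefore a poor fit. A restricted scheme would explain the four cohorts but not the fifth: with permuted blocks the largest imbalance is half the block size, so a difference of 13 needs a block of at least 26.

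**6. Weight of cohort 3.** In a within-cohort estimate each cohort has weight n₁n₂/(n₁+n₂): 6.74, 10.24, 6.39, 6.74, 10.74, total 40.86. The cohort 3 share is 6.39/40.86 = 15.6%.
A selection bias of b within cohort 3 shifts the pooled effect by 0.156 × b. The bias is assumed, since the document gives no evidence of its size: 0.25, 0.5 or 1.0 percentage points of HbA1c gives 0.04, 0.08 or 0.16, against the 1.0 that the trial was sized to detect.

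**7. Leaving cohort 3 out.** 79 − 9 = 70 and 90 − 22 = 68, so 138 remain. The standard error ratio is √(40.86/34.47) = 1.089, about 9% larger.

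**The case against.** The strongest reply is that nothing has been shown to be broken. The article states no blocking or other restriction, so forced balance is only an inference from four counts. The 0.029 belongs to a cohort singled out because it is extreme. With five cohorts it is about 0.10, and pairing of spouses raises the single-cohort figure further. Overall, 79 vs 90 is unremarkable (two-sided P = 0.44). A different ratio in one cohort is still random allocation, and a cohort term deals with it. All of this stands.

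A reader might therefore go too far by inferring that the counts show cohort 3 was not randomised, or that 9 vs 22 could not have arisen under the stated procedure. The document does not support that, because it does not say what the procedure was.

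A reader might also link the split to the recruitment change: "recruitment was slower than expected in year 1, so in year 2, we increased enrollment rates by recruiting subjects from the MOH Diabetes Clinic". That is speculation. Cohort 3 is said to have finished in year 2, the cohorts overlapped, and cohorts 4 and 5, also year 2, split 14/13 and 22/21. Nothing in the article suggests that sicker or less motivated people ended up as controls.

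It is also fair to say that sequence generation and sensitivity analyses are often left to the full protocol or the analysis plan, neither of which is shown. Their absence is not the point here. The point is that the stated rule and the reported counts disagree, and chance under either simple or tightly restricted randomisation fits the five cohorts badly as a set.

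**Conclusion.** The contradiction between the stated rule and the cohort 3 counts is real and unexplained. It calls for verification and does not establish that randomisation failed. The evidence is moderate: P = 0.029 for cohort 3 alone, weaker after allowing for five cohorts or for couples, set beside P of about 0.02 for the tight balance in at least four of five cohorts under simple randomisation. The probabilities assume 1:1 allocation and independent individuals, except where couples are modelled with an assumed number.

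If there was selection, its effect on the pooled estimate is limited by the 15.6% weight of cohort 3. Even an assumed bias of 1.0 percentage point of HbA1c within it shifts the result by about 0.16. If the split was random, there is no bias. The matter should be settled before analysis, and it is not a reason to discard the cohort.

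**What to change.** Before analysis:

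1. Check cohort 3 against the original allocation list and analyse each participant in the arm first assigned, as the planned intention-to-treat analysis already implies. State at what stage the 169 were counted. Removing cohort 3 leaves 138, and removing the 31 early losses also leaves 138; say whether this is coincidence.
2. Correct the counts if they are wrong. If they are right, correct the statement about approximately equal numbers and explain the split.
3. Make cohort a fixed term in the primary models, not an optional covariate. This handles a differing ratio but not selection between arms.
4. Prespecify a repeat of the HbA1c and fasting glucose analyses without cohort 3 (70 vs 68) and report it beside the pooled result.
5. If the list does not reproduce 9 vs 22, or cannot be found, state that cohort 3 departed from the stated procedure and interpret the pooled estimate accordingly. If the list confirms 9 vs 22 as randomised, the pooled analysis stands.

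The cost is a check of existing records and one further model run per endpoint. The sensitivity estimate has a standard error about 9% larger. Its 138 participants exceed the planned 120 before losses; if the 18% early loss fell evenly, about 138 × 138/169 = 113 would remain, slightly below 120, so it should be read for consistency and not as a second test.
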